### Methods: Data monitoring

Data monitoring is supervised by the Charité-BIH Clinical Study Center, which is independent of the study sponsor and has no competing interests. The trial will be stopped once the planned N is reached. Potential serious adverse events are monitored by the DSMC.

### Auditing

The coordinating center in Berlin provides organizational support and overview over all study related processes (e.g., enrollment, site status and other commitments). All processes of each subproject are determined in a standard operating procedure (SOP) and continuously reviewed by the study staff. Deviations from the SOP are documented (e.g., missing data, dropouts). Recurrent deviations are discussed in monthly meetings of all study staff members. Regular site monitoring visits (pre-study visits, initiation visits, and periodic monitoring visits) are conducted.

### Ethics and dissemination

#### Dissemination strategy

The research team will publish one primary outcome article, describing the effect of the group intervention on parenting and child abuse potential. Another publication will focus on the secondary gains achieved by the intervention, testing effects on the secondary outcomes named in the measurement section of this protocol. Additional analyses using variables assessed for the other subprojects will be published.

Exploratory analyses will be conducted to test for possible moderators (see above additional measures) of the intervention effect. If any variables make a meaningful contribution to explain the effects of the intervention on the primary or secondary outcomes, these analyses may result in further publications.

Results will be presented at national and international congresses and workshops.

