#### Additional measures

To analyze potential control variables such as maternal trauma and conflicts in partnership, the Childhood Trauma Questionnaire (CTQ; [50], German version; [51]) at day 0 and the Conflict Tactic Scale for Partners (CTS-P; [52]) (day 0, week 12, and month 9) are applied. As an additional exploratory aspect, maternal mentalization is assessed using the Parental Reflective Functioning Questionnaire (PRFQ; [53]) (day 0, week 12, and month 9).

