### Power analysis and sample size

Because the primary hypothesis concerns the investigation of the effect of the intervention in contrast to the waiting control group, power calculation is based solely on a repeated measure, within-between ANOVA. We strive for a statistical power of 99%; multiple-comparison problems are considered according to Cramer et al. [57]. A conservative estimate of *r* = 0.5 is used for the correlation between repeated measures of the same outcome to ensure enough power for outcomes with relatively low stability over time. Using the software G-Power, these specifications lead to a required sample size of 110 patients (2*55 per group intervention/waiting group) to detect an interaction when Cohen’s *f* for the interactions of 2*3 ANOVA is assumed to be moderate at 0.20. Based on our pilot groups, we assume that 10% of participants assigned to the intervention will not start intervention after assignment. Dropout rates from psychotherapy trials for BPD range between 22.3% and 28.2% [58]. In conclusion, we expect a dropout rate from baseline to follow-up assessment of 25%. Therefore, we assess *n* = 178 mothers with BPD for eligibility (*n* = 160 start the trial, *n* = 140 at post assessment, *n* = 120 at follow-up).

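### The dissemination plan ties separate publication of the exploratory moderator analyses to their result, with no threshold and no stated route for null results

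*Protocol article*

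**What the plan says.** The Dissemination strategy section of the protocol article lists four kinds of output.

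- Primary results: "The research team will publish one primary outcome article, describing the effect of the group intervention on parenting and child abuse potential". No condition is attached.
- Secondary results: a second paper on the secondary outcomes, also promised without condition.
- Other subprojects: "Additional analyses using variables assessed for the other subprojects will be published". Again no condition.
- Moderators: "Exploratory analyses will be conducted to test for possible moderators (see above additional measures) of the intervention effect". Carrying out these analyses is unconditional, but their separate publication is not: "If any variables make a meaningful contribution to explain the effects of the intervention on the primary or secondary outcomes", then "these analyses may result in further publications".

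The pool of moderators is the Additional measures section. It introduces trauma and partner conflict with "To analyze potential control variables such as maternal trauma and conflicts in partnership, the Childhood Trauma Questionnaire" (CTQ) and the partner version of the Conflict Tactic Scale (CTS-P). It introduces the PRFQ separately: "As an additional exploratory aspect, maternal mentalization is assessed using the Parental Reflective Functioning Questionnaire".

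The sample size section sizes the trial for the intervention effect over time: "power calculation is based solely on a repeated measure, within-between ANOVA".

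**The concern.** A moderator claim is usable only if the reader knows how many moderators were tried on how many outcomes. If a paper appears when some interaction looks interesting and nothing is said when none does, the published record is a filtered sample. Chance findings are over-represented, and the interaction sizes that pass the filter tend to be too large. This holds even when each test is done correctly and called exploratory, because that label says a result is tentative but not how many other tests lie behind it.

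At stake is the credibility of any later statement about which mothers benefit more or less, for example according to their own childhood trauma. The comparison of intervention with waiting control on the primary outcomes is not affected.

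**Working it through.** **Step 1: compare the publication commitments.** All four kinds of output sit in the same section. Three are promised outright. Only the moderator output has a condition, and that condition is what the analysis shows. No numerical or verbal threshold is given for it. The article describes no supplement, report or table in which moderator results would appear if the condition is not met.

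**Step 2: count the tests that the article's lists imply.** The article gives no count, so there is no stated figure to reproduce.

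- Moderators (Additional measures): CTQ, CTS-P, PRFQ = 3.
- Primary measures (Primary outcome measures): EFB-K, DEAPQ-EL-GS, CAPI, CTS-PC, CNI = 5.
- Secondary measures (Secondary outcome measures): Parenting Sense of Competence Scale, Parental Stress Index, DERS, BSI, QTF = 5.
- With one total score and one overall test per pair: 3 × (5 + 5) = 30.

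The count moves with the reading. If the PRFQ is an exploratory outcome and not a moderator, it is 2 × 10 = 20. If the CNI, which is rated by staff and trainers, is left out, it is 3 × 9 = 27. If week 12 and month 9 are tested separately, it is 3 × 20 = 60. Subscales would add more.

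**Step 3: chance findings with no true moderation.** The article states no level for these tests, so two-sided α = 0.05 is assumed. For k tests, the expected number of false positives is 0.05k. Under independence, P(at least one) = 1 − 0.95^k.

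| Reading | k | Expected | P(at least one), independent |
|---|---|---|---|
| PRFQ not a moderator | 20 | 1.0 | 1 − 0.95^20 = 64% |
| CNI not counted | 27 | 1.35 | 1 − 0.95^27 = 75% |
| All listed pairs | 30 | 1.5 | 1 − 0.95^30 = 79% |
| Two visits tested separately | 60 | 3.0 | 1 − 0.95^60 = 95% |

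**Step 4: allow for correlated outcomes.** The outcome instruments will correlate, but the article does not say by how much. Treat the test statistics for one moderator as equally correlated normal variables across the 10 outcomes, and the moderators as independent of each other. P(at least one) then becomes:

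| k | correlation 0.5 | correlation 0.7 |
|---|---|---|
| 30 | 64% | 51% |
| 20 | 49% | 38% |

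Correlation lowers the chance of at least one false positive but leaves the expected number unchanged.

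**Step 5: effect of the proposed change.** Full reporting does not reduce the number of chance findings. It shows the reader the denominator and the null results beside them.

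**The case against.** The strongest reply is that the sentence says less than a reader may take from it. It can be inferred that moderator results will be published only if positive and that nulls will be withheld. The text does not say so. It says when additional papers might be written, and null results could still appear in the primary or secondary article. That objection stands, so the point is confined to a result-dependent trigger with no stated alternative route.

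Second, the analyses are announced in advance, drawn from a named pool and labelled exploratory, and the primary inference is untouched. This also stands, and it limits the weight of the point. It does not remove it, because the label does not supply the number of tests.

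Third, the moderator model, the level and any multiplicity rule may sit in a statistical analysis plan that is not shown, and the sample size section says multiple comparisons are considered. Agreed: none of that is counted as missing. But the publication rule is stated in this article, and correct handling of each test elsewhere would not alter what the rule brings into print.

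Fourth, the figures are assumption-driven. A count of 30 is not settled, and the trigger might be an effect size and not a p-value. This is fair, and the figures are illustrative. An effect-size trigger would still select on the result, though its error rate cannot be computed from the article. For the same reason no inflation factor is given for published interactions: it would depend on an arbitrary choice of true effect.

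Finally, one might infer that moderator findings will decide who is offered the programme. The article links later roll-out to evidence that the training works, not to moderators, so this remains a possibility only.

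**Conclusion.** The point holds in a limited form. The dissemination strategy makes separate publication of the moderator analyses depend on their result, by an undefined criterion and with no stated route for nulls, while every other output is promised outright. Followed as written, it favours selective reporting of moderators.

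The size is illustrative: about 20 to 30 tests, 1.0 to 1.5 expected chance findings, and a 64% to 79% chance of at least one under independence, or roughly 38% to 64% with outcome correlations of 0.5 to 0.7. This rests on a two-sided 5% level, one test per pair, no true moderation and selection by significance. None of these is stated in the article.

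The documents do not support saying that null results will be suppressed, that exactly 30 tests are planned, or that the trial's main conclusion is at risk.

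**What to change.** Replace the conditional sentence in the Dissemination strategy with:

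*All moderator analyses conducted will be reported whatever their result, in a supplementary table with interaction estimate, 95% CI and the total number of tests, labelled exploratory; any separate moderator paper will refer to that table.*

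A multiplicity adjustment, such as false-discovery-rate control, is optional; full reporting is the part that matters.

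The cost is one changed sentence and one supplementary table. No new data are needed and the primary analysis is unchanged. The downside is that nominally significant moderators will stand out less.

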#### Ethical issues

Ethical approval for this RCT was obtained by the ethics committee of the DGPs (No. [name]2019-07-29VADM). The study is conducted in accordance with the Helsinki Declaration. The research team members have made sure that the study respects the following ethical principles: all the personal data gathered are treated confidentially, written informed consent is collected, data are securely stored and the data will only be used for research purposes. Participation in this research study is voluntary. Participants are reminded of their rights to withdraw from the study without giving any reason. Data privacy is guaranteed: all the research data gathered during the project is identified using pseudonyms. Personal data is being kept under lock and is stored separately from research data.

Standard operating procedures for all study procedures have previously been defined. Communications and publications will not enable the identification of individual participants.

### Protocol amendments

Any modifications to the study protocol which may impact on the conduct of the study, potential benefit of the participants or may affect participant safety (e.g., changes of study objectives and study design, addressed population, sample sizes, SOPs) will require a formal amendment to the protocol. Amendments need to be agreed upon by the BMBF (Federal Ministry of Education and Research) and approved by the Ethics Committee (DGPs) prior to implementation.

Minor corrections and/or clarifications that have no effect on the way the study is to be conducted are protocolled.

### Patient involvement

The group intervention has been developed in a continuous dialog with mothers with BPD. Before setting the design of the study, we conducted two intervention groups with all interviews, questionnaires, and assessments to check for feasibility and participant’s feedback. Participant’s feedback was incorporated in the final design.

## Conclusion

Main aim of this RCT is to evaluate a newly developed, disorder-specific parenting intervention for mothers with BPD. Using a longitudinal design, we expect the intervention to have a positive effect on parenting and to decrease the risk of child abuse (primary outcomes). Additionally, we hypothesized the intervention to reduce parental stress, enhance parental competence, improve maternal emotion regulation, and reduce mental distress (secondary outcome).

We expect the intervention to enhance the opportunity for a healthy child development. At best, in the long run, an interruption of the transmission of violence and emotion regulation is achieved.

### Access to data—Intra study data sharing

A cleaned data set will be provided by the Charité-BIH Clinical Study Center. All Principal Investigators will be given access to the data sets. Project data sets will be transferred according to the standard operating procedures (SOPs) defined for the project. All data sets will be password protected and blinded of any identifying participant information.

### Ancillary and post-trial care

In case of ancillary or post-trial needs of participants, study staff provides information, contact possibilities, or access to consulting (e.g., family counseling) and psychotherapy treatment (e.g., in- or outpatient facilities).

Should this study provide evidence of the effectiveness of the training, efforts will be made to establish the intervention in in- and outpatient facilities for mothers with BPD.

## Data Availability

Parts of the final anonymized trial data set will be available.
